#### Outcomes

All pre-screening measures took place in January and February (2014 for cohort 1 and 2015 for cohort 2). Baseline physical health and fitness assessments were conducted in the last week of February, at which point participants also completed questionnaires designed to measure demographic and background variables, physical activity, general health status, as well as a measure of participant personality. In weeks 2, 7, 12, 14, 19, and 24 of the intervention (March to August) participants completed questionnaires that included measures of cohesion, instrumental and affective attitudes, task and self-regulatory self-efficacy, stigma consciousness and psychological flourishing. At week 2 and 14 assessments the questionnaire battery also included measures of intra-group perceptual similarity, commute time, and commute mode. At week 7 and 9, the questionnaire battery also included measures of intra-group communication and group interaction processes. In weeks 12 and 24, the questionnaire battery also included measures of participants’ physical activity behavior outside of their respective YMCA programs. Measures of program adherence were obtained throughout the course of the respective six-month programs. At the end of the respective six-month programs, participants completed the same physical health and fitness assessments as those completed at baseline, at which point the process evaluation interviews were also conducted.

#### Measures

##### Demographic and background measures

Data related to a number of background and demographic variables were collected in relation to participants’ age, sex, country of birth, dwelling arrangements [42], post code (as a measure of socio economic position) [42], and employment/retirement status [43] as well as Canadian Census questions [44] for marital status, ethnicity, level of education, household income. We also collected measures related to participants’ commute time, and mode of transport, to the respective YMCA program.

##### General health status

Data were collected in relation to participants’ smoking status, general health status, previous history of illness, and current use of medication.

##### Physical activity adherence behaviors

Class attendance was objectively measured via reports generated by the use of participants’ YMCA access cards. These data will be used to determine attendance throughout the trial. With regard to the research question concerning the extent to which participants choose to re-enroll after the initial 3-month program has ended, program enrolment records were used (dichotomous: 1 = yes, 0 = no). We collected data at baseline related to participants’ physical activity behavior using Godin’s Leisure Time Exercise Questionnaire (LTEQ) [45], and at weeks 12 and 24 we collected measures related to participants’ physical activity behaviors outside of the program, using procedures described by Wilcox and colleagues [46].

##### Physical health and fitness measures

We collected data related to participants’ height, weight, body composition, blood pressure, functional fitness, and mobility. Specifically height was measured using a standiometer. Both weight (kgs) and body composition (percentage of body fat, as assessed through bio-electrical impedance) were measured using a commercially available portable body composition analyzer (Tanita Model TBF 300 GS, Tanita Manufacturing Co., Tokyo, Japan). Blood pressure was assessed using automatic blood pressure monitors (Life source UA-767 Plus, A&D Medical, USA). These monitors use the oscillometric method to simultaneously provide recordings of systolic (SBP) and diastolic blood pressure (DBP). Participants were required to remain seated for at least 5 min prior to all assessments. Three recordings were made, with an average taken for SBP and DBP. Mean Arterial Pressure (MAP) is calculated according the following equation: MAP = DBP + 1/3(SBP - DBP). Finally, participants completed the functional fitness test for older adults developed by Rikli and Jones [47]. This includes a battery of six tests that assess upper and lower body flexibility and strength as well as aerobic fitness via a 2-min step test. The activities performed during these tests are designed to reflect “the physiologic attributes that support the behavioral functions necessary to perform activities of daily living” (p. 133, [47]).

##### Psychological variables

The primary psychological cognitions targeted in the intervention related to group cohesion and affective attitudes (enjoyment). Class cohesion was assessed using the Physical Activity Group Environment Questionnaire (PAGEQ) [48]. The PAGEQ is a 21-item self-report questionnaire designed to assess four dimensions of cohesion within exercise classes; namely, attraction to the group’s task (ATG-T), and social (ATG-S) activities, as well as perceptions of group integration around the group’s task (GI-T), and social (GI-S) activities. The PAGEQ was developed specifically for older adults taking part in physical activity classes, with scores derived from this instrument found to demonstrate good reliability (α ≥ .72 [48]), factorial validity, and predictive utility. Affective attitudes (enjoyment) towards physical activity were assessed using the procedures described by Rhodes and Matheson [49]. Specifically, a 7-point semantic differential scale was used, with anchors including “Enjoyable—Unenjoyable”, “Pleasant—Unpleasant”, “Interesting—Boring.” Previous research with older adults has found support for both the internal consistency and predictive utility of scores derived from this instrument [49]. In addition to the two primary psychological variables targeted in the intervention (i.e., cohesion and affective attitudes), data were also collected on a secondary set of psychological variables related to participants’ (a) personality [50], (b) task self-efficacy [51], (c) barriers self-efficacy [52], (d) instrumental attitudes [49], (e) stigma consciousness [53], (f) intra-group communication and group interaction processes [54], (g) psychological flourishing [55], and (h) within class perceptual similarity [17, 20].

##### Process evaluation

A process evaluation was conducted to provide insights into both *content fidelity* (“what is done”) and *process fidelity* (“how it is done”) with regard to intervention delivery, as well as the extent to which the intervention meets with the needs of those involved (i.e., older adults) in the program [35]. Without any assessment of intervention fidelity internal validity is potentially compromised [35]. Furthermore, as Plummer and colleagues [56] suggest, process evaluations “can help explain the program’s outcomes and identify ways to improve and/or replicate it. For example, if there are unsatisfactory outcomes, it is important to understand whether this could be due to poor program design, inadequate implementation or special contextual factors.” (p. 500).

In the GOAL Trial, interviews with program participants will enable us to appraise the specific subcomponents of the program and, where appropriate, further modify these for future initiatives [57]. Semi-structured interviews were used that allow us to examine each of the underlying principles of the program (e.g., effects of intra-group age and gender composition, perceptions of class instructor). One of the project coordinators (author [name]) conducted the interviews with participants, and although qualitative data analysis will be overseen by the principal investigator, the coding will be performed by research assistants (i.e., unconnected with the intervention activities) [58].

#### Sample size

We powered our study to detect significant differences in individuals’ physical activity adherence (over 3 and 6 months) in the SASG groups when compared to the SAMG and MAMG standard care control condition. In order to detect a medium effect size *f* = .25 (difference between the SASG and both SAMG and MAMG conditions) based on a 2 (Gender) x 3 (Conditions) ANCOVA with the percentage of classes attended over three and six months specified as dependent variable (while controlling for baseline levels of physical activity) with power (1 - β) set at .80, and alpha set at .05, 211 participants were required across the 3 centers [59]. In order to conduct a logistic regression analysis based on individuals’ re-enrollment across the three group-based programs, based on power at .80, alpha at .05, an anticipated medium effect size (odds ratio = 2.5), and a balanced design, 167 participants were required [59].

To test for mediation through use of a cross-lagged panel model based on a structural equation modeling (SEM) approach, while modeling gender invariance, we drew from three broad criteria. First, based on recommendations provided by MacCallum et al. [60], and using Preacher and Coffman’s [61] R-code for assessing RMSEA (< .05), based on power set at .80, a minimum sample size of 163 was identified as being necessary for conducting the cross-lagged panel model (without considering gender differences). This calculation approximates with recommendations provided by Garver and Mentzer [62] that a ‘critical sample size’ of 200 is required as a general rule of thumb for providing sufficient statistical power for SEM analysis. In addition to these two sets of considerations, in light of the fact that the panel model will include a *multi-group* (males, females) component in order to examine gender invariance, this requires twice the sample size (i.e., *n* = 326, cf. MacCallum et al.; *n* = 400, [60]). Thus, in order to account for an attrition rate as high as 25 % (over the course of the program) a sample size of 540 would be sufficient to examine the mediational model proposed in this trial. In sum, we determined that an overall sample size of 540 older adults across the three arms of the trial would be sufficient for examining each of the study hypotheses.

For the process evaluation component of the trial 15 participants per experimental condition (*n* = 45 in total) will be invited to participate in a semi-structured interview designed to evaluate each of the three experimental conditions (group-based programs) embedded within our trial. It has been suggested that such a sample size is generally sufficient to ensure data saturation with qualitative interview-based data [63].

### Recruitment

Participants were recruited via advertisements placed through the local media, recreation centers, health care centers, hospitals, physician general practices, shopping malls, golf courses, and online interest sites within the Lower Mainland of British Columbia. Eligibility criteria were such that participants must be 65 years of age or older (both males and females) and did not have any contraindications which might prevent that person from participating in moderate-intensity physical activity. We intended to recruit an equal proportion of males and females. Interested persons were asked to call the trial hotline to inquire about program details. The GOAL Trial hotline was used for a pre-screening procedure.

#### Proposed outcome analyses

Preliminary analyses will be conducted to examine whether any patterns of missing data exist (e.g., missing at random, missing completely at random, etc.) for each of the psychosocial variables (cohesion, affective attitudes) using the Missing Value Analysis (MVA; examination of Little’s chi square test) on SPSS Version 20. The data will also be examined for multivariate and univariate outliers, as well as for violations of normality, with the appropriate transformation procedures utilized. Prior to the main analyses, we will also examine invariance in the primary outcome variable (adherence over 3 and 6 months) across the two cohorts (cohort 1 – March to August 2014; cohort 2 – March to August 2015). In light of the fact the two cohorts will be examined at exactly the same time of year, using exactly the same experimental procedures, we would expect invariance in patterns of adherence across the three conditions in each year, thus supporting the pooling of data from both cohorts. Two 2 (gender) x 3 (conditions) ANCOVAs with baseline measures of physical activity (LTEQ scores) entered as a covariate, and adherence to the program over 3-months and 6-months as the dependent variable.

A logistic regression analysis will be conducted to examine the likelihood of older adults randomized to the SASG condition re-enrolling in the same SASG condition after the initial 3-month program, when compared to the re-enrollment of older adults in the SAMG and MAMG conditions. In the logistic regression model, gender will be added as an independent variable, with the regression model explained by $$ \pi =\frac{1}{1-{e}^{-x}} $$ where x = *b0* + *b1G1* + *b2 G2* + *b3 gender* + *b4G1*gender + b5G2*gender* (where *b0* is the intercept and *b1*-*b5* are the slopes for predictors). For hypotheses 1, 2, and 4, SPSS Version 20 will be used to analyze the data.

Mediation will be tested through use of a multi-group (to examine whether the effects are invariant across gender) cross-lagged panel model using a structural equation modeling (SEM) framework. Cross-lagged panel models are a type of auto-regressive modeling. This approach was proposed by Cole and Maxwell [64] for longitudinal data and will be adapted for the purpose of the present study. This approach has two advantages. Specifically, it allows us to examine the reciprocal relations between the mediators (cohesion and affective attitudes), and the outcome (adherence). In a recent paper we indicated the importance of assessing group cohesion throughout the lifespan of a physical activity group, and not just through a single time-point early-program measure (this has been the most commonly used method of assessing cohesion as a mediator within group dynamics physical activity research [65]). This panel modeling approach, in which all the variables are measured at multiple time points, can rigorously test the prospective relations between predictors (assignment to experimental condition), mediators, and outcomes (i.e., predictors prior to mediators and mediators prior to outcomes). The cross-lagged panel model will be estimated using Mplus 7.2 with a full information maximum likelihood (FIML) estimator used to handle missing data [66]. This procedure will use all available data points for parameter estimation under the assumption that the data are missing at random. FIML estimation tends to produce less biased estimates than deletion or simple missing data imputation techniques (e.g., EM algorithm, regression, listwise/pairwise deletion, mean replacement) even when data are not missing at random [67]. By examining multi-group models, this will allow us to examine whether the structural pathways are invariant across genders.

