### Study interventions

The trial is taking place at three different YMCA centers in the Lower Mainland of British Columbia, over 2 years. The group exercise classes take place in 3-month blocks with the opportunity to re-enroll in the same program for another 3 months, thus lasting 6-months in total (see Fig. 1). Each program is run on the basis of classes taking place three days per week, with classes lasting 50–60 min. This dosage (150–180 min/week) is consistent with Canada’s current physical activity guidelines for older adults engaging in ≥ 150 min of moderate-to-vigorous physical activity per week [38], as well as findings from the Canadian Community Health Survey [39] which found that 67 % of seniors who are active three or more times a week are in good health, compared to 36 % who are infrequently active.

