#### Program structure

The intervention group classes were developed with the intent of fostering an engaging environment that reflects sound group exercise classes [41]. That is, the research team purchased music playlists that had the appropriate beats per minute (BPM) to align with warm-up/cool-down (120–134 BPM) and moderate intensity physical activity (135–160 BPM). Further, a website was developed to provide instructors (and class participants) with audio, written, and visual (i.e., videos) tutorials for completing exercises that were performed in the sessions. These tutorials made explicit use of both male and female older adult models to demonstrate correct posture and form.

As with the *Lively Lads* program*,* similar-aged volunteer instructors lead the GOAL Trial exercise classes. Instructors were recruited via local media, flyers at the partnering YMCA, and word of mouth. In addition, for the second year of the trial we recruited former participants (from the first cohort) who had expressed an interest to continue as volunteer instructors for the second cohort. Instructors were provided training, through three modules, at one of the three participating YMCAs related to ‘Program Basics and Guidelines’, ‘Tailoring the Program’, and ‘Instructor Mastery’. This training was guided by a Manual of Procedures (available from the first author on request). In the ‘Program Basics and Guidelines’ module, instructors were informed of the study goals and the underlying theoretical principles in lay terminology. They also completed a facility orientation (including First Aid procedures). In the ‘Tailoring the Program’ module, volunteer instructors learned of the different experimental conditions and how to modify the program specific to the SASG or SAMG composition of their group. Finally, instructors had the opportunity to practice leading a group (of the other volunteer instructors) in an exercise class in order to develop their confidence and comfort with the exercises. The duration of volunteer training depended on instructors’ level of certification and previous experience; however, 45 hours of instruction were available.

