There are a few potential limitations to address at the onset. First, the MAMG is unique in that participants can choose any 3-day per week class offered at the YMCA. From a design perspective, there may be a limitation in giving MAMG participants choice in terms of which YMCA course they wished to participate, since participants in the SASG and SAMG conditions were not given any such choice. However, from a pragmatic perspective, we believe that the MAMG group represents the most appropriate type of control condition as it reflects the typical type of exercise class available within community exercise settings. Thus, MAMG provides a strong point of comparison.

There may also be critique of variation related to class leaders. Measures were taken in the extensive training of the volunteer, similar-aged instructors. All volunteer leaders were trained at the same time, through the three modules outlined above. In this way, we sought to increase the likelihood of treatment fidelity across all conditions at each site. However, there may be some inherent differences based on instructor personalities, level of exercise instructor experience, and so forth. To account for these potential differences across conditions and sites, the process evaluation includes queries about perceptions of the class leaders (e.g., leadership and communication style).

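### Pooling of the two cohorts is supported by a weak preliminary check and an overstated claim of identical procedures, and the written-out models contain neither cohort nor site

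*Protocol article*

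**What the plan says.** The Participants section sets two cohorts of 270, March to August 2014 and March to August 2015. The Study interventions section adds the sites: "The trial is taking place at three different YMCA centers in the Lower Mainland of British Columbia, over 2 years".

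Under Proposed outcome analyses, invariance of 3- and 6-month adherence across cohorts is to be examined before the main analyses. The authors reason from the shared season and from "using exactly the same experimental procedures" that "we would expect invariance in patterns of adherence across the three conditions in each year, thus supporting the pooling of data from both cohorts". No test, significance level, equivalence bound or unpooled alternative is named.

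The same section then gives the models. Adherence is analysed by "Two 2 (gender) x 3 (conditions) ANCOVAs with baseline measures of physical activity (LTEQ scores) entered as a covariate". Re-enrollment is analysed by a logistic equation with an intercept and five slopes: two condition terms, gender, and the two condition-by-gender products. Cohort and site appear in neither.

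On delivery, the Program structure section states that "for the second year of the trial we recruited former participants (from the first cohort) who had expressed an interest to continue as volunteer instructors". The Discussion states that "All volunteer leaders were trained at the same time".

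**The concern.** Three things bear on pooling.

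- **The stated ground.** A pool of former participants could not have existed in cohort 1. Volunteer instructors lead SASG and SAMG, whereas MAMG participants join the regular YMCA classes. The change could therefore act on the cohort-by-condition pattern, which is what the article expects to be constant.
- **The evidence the check can provide.** Failing to find a cohort difference says little unless the check had a good chance of finding one.
- **The models.** Cohort and site are known for every participant. Leaving them out puts whatever variance they explain into the error term and leaves any chance imbalance between arms unadjusted.

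At stake are some precision and a clear statement of the main analysis. As written, a reader cannot tell what would happen if the cohorts looked different.

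**Working it through.** **Inputs from the article.** Cohen's f = .25, power .80, alpha .05 and N = 211 (Sample size); 270 + 270 = 540 participants and 3 centers; attrition up to 25%, so 540 × 0.75 = 405.

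**Method.** Noncentral F with noncentrality λ = f² × N, and denominator df = N − cells − covariates.

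**Step 1: the plan's own figure.** The article says "In order to detect a medium effect size *f* = .25", and that with power "set at .80, and alpha set at .05, 211 participants were required across the 3 centers". With numerator df = 5 (all six gender-by-condition cells) and one covariate, N = 211 gives λ = 0.0625 × 211 = 13.19, denominator df = 211 − 6 − 1 = 204 and power 0.800. N = 210 gives 0.798. The stated 211 is reproduced.

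**Step 2: f = .25 in SD units.** Assume that SASG differs by d from both other arms, which are equal. The cell deviations are 2d/3, −d/3 and −d/3, with mean square (4 + 1 + 1)d²/27 = 2d²/9. So f = d√2/3, and d = 0.25 × 3/√2 = 0.53 SD. Applying f = .25 to the condition effect in this way is an assumption.

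**Step 3: power of a cohort-by-condition test.** If the SASG effect differs between cohorts by δ, the interaction deviations are half as large, so f = δ√2/6. The test has 2 numerator df, 12 cells (gender × condition × cohort) and one covariate. Denominator df is 527 at N = 540 and 392 at N = 405.

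| Assumed cohort-2 effect | δ (SD) | f | λ, N = 540 | Power, N = 540 | λ, N = 405 | Power, N = 405 |
|---|---|---|---|---|---|---|
| Halves to 0.27 SD | 0.265 | .0625 | 2.11 | 0.23 | 1.58 | 0.18 |
| Vanishes | 0.53 | .125 | 8.44 | 0.74 | 6.33 | 0.60 |

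For other assumed interaction sizes, power at N = 540 and N = 405 is 0.16 and 0.13 at f = .05, and 0.53 and 0.42 at f = .10.

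These figures treat observations as independent. Clustering by class would lower them.

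**Step 4: cost of adding cohort and site.** Cohort takes 2 − 1 = 1 df and site 3 − 1 = 2 df, 3 in total.

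- The required N stays at 211 (denominator df 201, power 0.800).
- Power for the 2-df condition effect at f = .25 stays at 0.908 for N = 211 and 0.997 for N = 405.
- If cohort and site explained an assumed 2%, 5% or 10% of residual variance, f would become .25/√(1 − R²) and the required N would be 207, 201 or 191.

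**Step 5: the passages on delivery.** The Program structure section adds one instructor source in year 2. It gives no number and does not say that earlier instructors were replaced. Season, class frequency and length, training modules and outcome measures are described the same way for both years. The conflict with the claim of identical procedures is therefore confined to instructor source. The Discussion's sentence on training cannot literally cover both 2014 instructors and people who were still participants in 2014. It sits beside a stated aim of fidelity across conditions and sites, so joint training within each year is a possible reading.

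**The case against.** A reader might infer that the article makes pooling depend on a non-significant test. It does not say so. It speaks of examining and expecting invariance, names no test or threshold, and states the ANCOVAs without condition. A missed interaction would also lead to the same pooled analysis recommended here, so low power does no damage by that route. This objection stands. What remains is that the check is offered as support for pooling, is weak support for modest differences, and comes with no stated consequence if it fails.

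A reader might also infer that the three centers ran different timetables. The article does not state this and describes a common three-day schedule for the intervention classes.

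It is also fair to say that a new instructor source need not be a new experimental procedure, that MAMG's use of ordinary classes is the same in both years, and that no cohort or site variance is given. The scenarios above are therefore assumptions, and 74% power for a vanished effect is not trivial. Randomization of individuals means that leaving out cohort and site does not by itself bias the comparison. These points limit the size of the concern.

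The omission cannot be put down to condensation for a journal, because the factors, the covariate and every logistic term are written out.

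**Conclusion.** The point holds in a limited form. The claim that procedures were exactly the same is too strong, given the year-2 instructor source in the SASG and SAMG arms. The invariance check is weak support for pooling: 23% power (N = 540) or 18% (N = 405) if a 0.53 SD effect halves, and 74% or 60% if it disappears. These figures rest on assumed effect changes, equal cells and independent observations.

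Omitting cohort and site loses whatever precision they offer and leaves chance imbalance uncorrected. The gain from including them is unknown but nearly free: 3 df, no change in the required 211, and 207 to 191 if they explained 2% to 10% of residual variance. The documents do not support a claim of biased treatment comparisons or of an inadequate sample size. This is a worthwhile correction to the analysis wording, and it does not threaten the trial's validity.

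**What to change.** 1. State that both cohorts will be analysed together whatever the invariance check shows.
2. Add cohort (2 levels) and site (3 levels) as fixed factors to the 3-month and 6-month adherence ANCOVAs and to the re-enrollment logistic model.
3. Report cohort-by-condition estimates with confidence intervals, labelled descriptive.
4. Replace the claim of identical procedures with a statement that names the year-2 instructor source and the arms it affects.
5. Say whether training at the same time means within each year.

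**Cost.** Analysis wording and 3 degrees of freedom, using data already held. In the logistic model the odds ratio becomes conditional on cohort and site, which should be stated when it is reported. The Trial status section says that no data from either cohort have been analysed, so the change can be made without knowledge of results.
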